### Objectives

#### Primary objective

The main objective of this study is to evaluate the performance of the epigenetic clock expressed as *epigenetic age acceleration (epigenetic clock age–chronological age)* in predicting all-cause mortality in a cohort of MM older patients.

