### Statistical analysis

Baseline characteristics will be described using standard descriptive methods, such as summary statistics and frequency tables. Parametric and non-parametric statistical approaches (such as contingency table analysis, regression, and analysis of variance) will be used when appropriate.

Data pre-processing will be performed using the R package *minfi* (56) and a DNA methylation level will be summarized for each CpG site by calculating a “*beta*” value ranging from 0 to 100%. CpG probes will be treated as missing if the detection *P*-value > 0.01, and CpG sites with more than 5% missing data will be excluded from the analysis.

Epigenetic age will be calculated by multiplying beta values by the regression weights from Horvath [353 CpG sites (35)], Hannum [71 CpG sites (37)], and Levine [513 CpG sites (38)] to create the respective clocks. Delta age (Δage) will be defined as a simple subtraction of the chronological age from the epigenetic age using all the versions of the clock mentioned previously. In all cohorts, cell count predictions will be estimated from DNA methylation data using the Houseman method (57).

The determinants of overall 10-year survival will be calculated using Cox proportional hazards analysis including Δage as independent variables, and corrected for the following confounders: age, gender, clinical, functional, or biological data. The accuracy of exposure variables in predicting mortality will be estimated using Harrell's C-statistics. The same analyses will be repeated by adding the individual age-associated CpGs (one at once) to the Cox model. A two-stage approach will be adopted to validate individual CpG sites associated with mortality. Initially, all of the more than 850,000 methylation sites analyzed by the Illumina Infinium MethylationEPIC Array will be analyzed in a proportion π_sample_=25% of the study sample in stage 1 (*n* = 272), and the results of stage 1 will be used to select a proportion of these *M* CpG sites (Ω_marker_) for follow-up on the remaining sample in stage 2 (75%, n=798). The parameter Ω_marker_ will be selected on the basis of the corresponding *p*-values within the context of the survival analysis.

The validity of the estimated coefficients will be internally verified using a non-parametric bootstrapping resampling analysis with replacements.

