In order to reduce the complexity of MM, a dimensionality reduction approach will be performed by clustering patients into a few groups on the basis of the most frequent diagnoses at baseline for each stratum in order to obtain a classification of patients according to an MM pattern. The risk analysis will be repeated for each MM pattern. The association between the epigenetic clock and MM patterns will be determined by means of a Generalized Linear Model. Multiple adjusted models will be developed to consider each possible covariate that could influence the significance of the results and to identify independent variables linked to primary and secondary outcomes. Survival analysis with Kaplan Meier estimates will be performed to assess and compare survival over time among the clusters (Log-Rank test). Cox proportional hazards models will be used to assess and compare survival-time outcomes in each cluster in the presence of possible confounders. Several network medicine-based approaches will be developed in order to build the Human Interactomes and Disease Networks (58). Finally, we will investigate the additive effect of the epigenetic clock on the predictive ability of MM patterns. Changes in Harrell's C and the categorical Net Reclassification Index (NRI) will be calculated with 1,000 bootstrap samples to estimate the 95% CI. A two-tailed *p*-value of < 0.05 will be considered statistically significant. The Bonferroni correction for multiple comparisons will be applied to control for the risk of false-positive results. Statistical analyses will be conducted using the Stata 15.1 Software Package for Windows (Stata Corp, College Station, TX).

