The availability of a comprehensive longitudinal database in synergy with new biomarkers will also allow us to evaluate how and which inappropriate drug decision-making could lead to the onset of new comorbidities or to functional impairment. Disentangling the relationship between polypharmacy and associated disease outcomes could prevent the onset of new chronic conditions and their relative costs for the National Health System, as well as improve the quality of life of older adults. Providing precise, personalized care is the cornerstone of health services designed for MM patients.

We also aim to construct an accurate, multicomponent algorithm that is inclusive of clinical, functional, and molecular data, capable of predicting at an early stage the onset of new comorbidities, death, and functional decline within 10 years of follow-up. Once validated, this tool could be made available to primary care practitioners for the screening, early diagnosis, and treatment of MM patients, thereby decreasing risks to individuals.

Our study's longitudinal design will also enable us to evaluate the quality of care provided to MM patients and to develop new multidisciplinary personalized care plans based on their clinical, functional, and biological profile. On the basis of the projected risk of adverse health outcomes, tailored, coordinated, and integrated treatment and long-term follow-up strategies will be formulated for each patient. This study will support an integrated health system built around systems medicine and strategic partnerships to manage MM. It could include: (i) an understanding of the social, economic, environmental, epigenetic determinants, molecular, and cellular mechanisms underlying MM; (ii) primary care and practice-based interprofessional collaboration; (iii) carefully phenotyped patients; (iv) the development of unbiased and accurate biomarkers for multiple morbidities, severity, and follow-up of patients; (v) socioeconomic science; (vi) development of guidelines; (vii) training; and (viii) policy decisions.

This approach is expected to improve the implementation of involved personalized medicine in clinical practice to reduce unfavorable outcomes and the deterioration of health conditions in the older population, improve access to healthcare services, and consequently, reduce healthcare expenditure.

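### Harrell's C and categorical NRI cannot by themselves show that a multi-marker model's projected risks are accurate; calibration should be reported with them

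*Protocol article*

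**What the plan says.** The Primary objective concerns how well epigenetic age acceleration performs "in predicting all-cause mortality in a cohort of MM older patients". The Statistical analysis section of the protocol article gives the measures. For exposure variables: "The accuracy of exposure variables in predicting mortality will be estimated using Harrell's C-statistics". For the clock added to multimorbidity patterns: "Changes in Harrell's C and the categorical Net Reclassification Index (NRI) will be calculated with 1,000 bootstrap samples to estimate the 95% CI". No risk categories for the NRI are given.

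The same section bootstraps the model coefficients. Phase V validates the selected biomarkers in the remaining 798 patients. Neither step is described as a check of predicted risks. The Kaplan-Meier curves compare clusters with each other, not observed with predicted mortality. Calibration, a calibration slope and a Brier score are not mentioned.

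The Discussion sets out the intended product and use. "We also aim to construct an accurate, multicomponent algorithm that is inclusive of clinical, functional, and molecular data" names the product. "Once validated, this tool could be made available to primary care practitioners for the screening, early diagnosis, and treatment of MM patients" gives a possible later use. A further sentence carries no such condition: "the projected risk of adverse health outcomes, tailored, coordinated, and integrated treatment and long-term follow-up strategies will be formulated for each patient".

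**The concern.** Planning care from a patient's projected risk needs risks that are right in size: among patients told 40%, about 40% should die. Ranking patients correctly does not ensure this.

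Harrell's C counts concordant pairs. Any strictly increasing transformation of the risks leaves every pair as it was, so C does not move however wrong the risks become. Categorical NRI does use the size of the risks, but only through the categories they fall in. If one model spreads its risks too widely, more events move up and more non-events move down, and NRI can report this as improvement although nothing new is known about any patient.

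Over-wide risks are what overfitting produces. The plan screens more than 850,000 CpG sites by p-value in 272 patients and then, in Phase VI, combines the validated markers with clinical, functional and biological data. If such a model were reported with C and NRI alone, the claim that its projected risk is accurate would have no support.

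**Working it through.** **1. The plan's own inputs.** The Sample size section gives a median survival of 6.2 years, HR 1.23, α = 0.05, β = 0.2 and 10 years. With exponential survival:

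- Reference 10-year mortality: 1 − exp(−10 × ln 2 / 6.2) = 67.3%.
- With HR 1.23: 1 − (1 − 0.673)^1.23 = 74.7%.
- Mean for equal groups (assumed): 71.0%.
- Freedman's formula needs 738 deaths; 738 / 0.710 = 1,039, within 3% of the planned 1,070. At 1,070 (about 760 deaths) Schoenfeld power is 81.4%.

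The sample size is therefore not in dispute. About 71% serves as the event rate in step 2.

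**2. What the two measures can and cannot see.** Risk = 1 − exp(−exp(a + s × lp)), with lp normal. s = 1 is the correct model; s > 1 stretches the same linear predictor, so the ranking is identical. NRI = [P(up | death) − P(down | death)] + [P(down | survival) − P(up | survival)]. Assumed: SD of lp 0.9 (C about 0.71), 400,000 patients, and a solved so that mean risk is 71% for every s.

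| Stretch s | Implied slope (1/s) | Change in C | Lowest decile, predicted / true | NRI, cut-offs 60/80% | NRI, cut-offs 50/75/90% |
|---|---|---|---|---|---|
| 1.25 | 0.80 | 0 | 20.1% / 26.1% | +0.020 | +0.081 |
| 1.5 | 0.67 | 0 | 15.6% / 26.1% | +0.030 | +0.128 |

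At s = 1.5 the Brier score worsens from 0.1506 to 0.1544 while NRI is positive.

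A second run assumed SD 0.5 (C about 0.63), the reference median of 6.2 years (event rate about 67%) and a doubled spread. Brier worsened from 0.196 to 0.207, yet NRI at 50/80% was +0.138. At n = 1,070 its 95% sampling range was +0.07 to +0.21, positive in all 300 runs.

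The sign is not universal. With one cut-off at the event rate, NRI for a wrong spread was about 0. Uniform under-prediction (mean predicted 50.3%, observed 66.7%) gave −0.056 at 50/80% but +0.197 at 20/40%.

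**3. The comparison the NRI sentence plans.** Nested Cox models with and without one useless added marker were fitted to the same data: n = 1,070, median 6.2 years, censoring at 10 years, 10 to 30 covariates, SD 0.5 or 0.9, cut-offs 50/80%, 200 runs each. Mean apparent NRI was +0.000 to +0.002 (SD about 0.01). The calibration slope in new data was 0.83 to 0.96. At n = 798 slopes were 0.78 to 0.96 and NRI at most +0.004. So the effect in step 2 does not carry over to adding one clock.

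**4. Multi-marker models.** Adding 10 to 60 noise markers picked in 272 patients and refitting in all 1,070 gave slopes of 0.82 down to 0.54 and apparent NRI of +0.10 to +0.25. Here the slope shows the fault and the NRI presents it as a gain. This is an upper illustration, because stage 2 is meant to drop markers that do not validate.

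**The case against.** The strongest reply is that Methods and Discussion concern different objects. The NRI sentence answers a bounded question, the clock's addition to multimorbidity patterns. The clocks use published weights, and single CpG sites enter the Cox model one at a time. The multicomponent algorithm is a Discussion aim, and its release to primary care is conditional on validation. The article also condenses a longer plan that may add calibration.

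Much of this stands. A reader might infer that the plan's NRI will reward a useless clock, or that a model with wrong risks would pass. The documents support neither: step 3 gives an NRI of about zero for one marker, and no pass criterion is stated. A reader might also take the 10-point error and the NRI of +0.03 to +0.13 as estimates for this study. They come from an assumed stretch and assumed cut-offs. The article speaks of projected risk, not absolute risk, and nothing in it rules calibration out. A Cox model is also close to calibrated in its own development data.

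It does not remove the point. The article fixes its performance measures down to the number of bootstrap samples, and that set does not match the stated use. The validation condition comes without a criterion, and the sentence on individual care plans is unconditional. Phase VI does build models from many markers, where step 4 shows the fault can be large.

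**Conclusion.** The point holds in limited form. C, its change and categorical NRI cannot support a claim that projected risks are accurate. C is unchanged by any rank-preserving error; this is exact and needs no assumption. That NRI can reward over-wide risks is shown by simulation and depends on cut-offs and type of error.

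The size depends on the model. For one fixed-weight clock added to multimorbidity patterns, the risk of a misleading NRI is negligible. For models with selected CpG sites and many covariates it is real, with slopes perhaps as low as 0.54 in the upper illustration. All simulated figures rest on assumed log-hazard spreads, cut-offs and exponential survival, since the article gives no spread or categories.

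The Cox association of Δage with mortality and the sample size are untouched. This is a change that should be made; it does not invalidate the study.

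**What to change.** In the Statistical analysis section, add for both the clinical model and the biomarker model:

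- Calibration slope, calibration-in-the-large, and observed (Kaplan-Meier) against predicted 10-year mortality by risk group.
- Correction for optimism by one of two routes: the planned bootstrap with marker selection repeated inside each resample, or evaluation in the stage 2 patients with coefficients fixed from stage 1. The first route needs the candidate sites in every resampled patient; if stage 2 measures only selected sites, the second is the practical one.
- Shrinkage of the coefficients if the slope is below 1, before any projected risk is reported.
- NRI computed only from calibrated risks.

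In the Discussion, make statements about using projected risk conditional on these results. Calibration in this cohort would not by itself cover primary care, because Strengths and limitations expects higher mortality in these hospitalised patients than in community dwellers.

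The cost is some extra analysis on data already planned. Reported NRI and accuracy may be less favourable.

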### Phase V: Validation of biomarkers in the entire study population (stage 2)

The biomarkers selected in phases IVa and IVb will be validated on the remaining samples (75%, *n* = 798).

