### Sample size

The sample size was calculated on the basis of the primary objective (the association between the epigenetic clocks' Δage and mortality). For this reason, we planned to include 1,070 samples of individuals from the Reportage Project. This sample was obtained by setting α = 0.05, β = 0.2, and using a Hazard ratio = 1.23, a 10-year follow-up period, and a median survival time of 6.2 years for patients whose Δage was not expected to increase. This sample size is also in line with other study populations in which the prognostic value of several epigenetic clocks were assessed (36). This sample will enable the detection of significant associations between epigenetic clock Δage and mortality during the 10-year follow-up period.

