One limitation of the study is that the sample size could be smaller than required to detect weak associations between the measured biomarkers and potential modifiers of the association between epigenetic age acceleration and mortality risk during the follow-up period. The sample size was designed on the basis of the primary objective of discovering significant associations between epigenetic clocks' Δage and mortality during the 10-year follow-up period. However, due to the number of potential tested modifiers, the Bonferroni correction for multiple comparisons will be applied to prevent false-positive findings. This study will recommend introducing several biomarkers in clinical settings to improve the prognostic value of MM. However, this translational protocol necessitates several estimation and validation phases. A limitation of the project could be the feasibility of a wide-scale implementation of these biomarkers in clinical practice. Nonetheless, the involvement of the most important stakeholders and companies would make it possible to develop new diagnostic and prognostic experimental procedures.

The absence of information regarding the causes of death of patients who died outside of hospital may also be considered to be another limitation of the study. For this reason, the association analysis on causes of death will only be utilized for descriptive purposes and will not be used in the main analyses in order to eliminate their potential influence on the outcomes.

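### Bonferroni is valid as stated, but Holm's step-down procedure gives the same 5% family-wise guarantee, never rejects fewer hypotheses, and would be a cheap refinement

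*Protocol article*

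**What the plan says.** Statistical analysis sets a two-tailed *p*-"value of < 0.05 will be considered statistically significant" and then adds: "The Bonferroni correction for multiple comparisons will be applied to control for the risk of false-positive results". Strengths and limitations returns to the subject: "due to the number of potential tested modifiers, the Bonferroni correction for multiple comparisons will be applied to prevent false-positive findings". That clause stands in the paragraph conceding that the sample could be too small for weak associations of biomarkers and modifiers. No other multiplicity method is named. The article does not say which tests form a family.

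The places where several tests arise are three epigenetic clocks (Statistical analysis), six named plasma proteins (Protein variables), more than 850,000 CpG sites screened in stage 1 (n = 272), the markers carried to stage 2 (n = 798), and an unstated number of modifiers. Stage 1 selection of CpG sites is described only as based on p-values. Phase V gives no significance rule for validation.

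Sample size works at the unadjusted level: "This sample was obtained by setting α = 0.05, β = 0.2, and using a Hazard ratio = 1.23".

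**The concern.** Without further qualification, Bonferroni means that each of m tests is compared with alpha/m. Holm orders the p-values and compares the smallest with alpha/m, the next with alpha/(m-1), and so on, stopping at the first failure. Both hold the family-wise error at alpha under any dependence, and every Bonferroni rejection is also a Holm rejection. The stated purpose, control of false positives, is therefore met equally by a method that is never less powerful.

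This matters a little more here than usual because the article itself concedes limited power for some of the corrected tests, and because Phase VI takes forward only biomarkers that were validated in stage 2. If a correction is applied at that step, a real marker missed by a small margin drops out of the integrated model.

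**Working it through.** **1. The plan's own sample size.** Inputs from Sample size: alpha 0.05, power 80%, hazard ratio 1.23, ten years of follow-up, "a median survival time of 6.2 years for patients whose Δage was not expected to increase". My assumptions: two-sided test, 1:1 split, exponential survival.

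- Events (Schoenfeld): 4(1.960 + 0.842)² / (ln 1.23)² = 733. Freedman's formula gives 738.
- Ten-year death probability: 1 - exp(-ln 2 × 10/6.2) = 0.673 in the reference group and 0.747 at hazard ratio 1.23; mean 0.710.
- N: 733/0.710 gives 1,033 and 738/0.710 gives 1,040. With the reference probability 0.673, N is 1,090 or 1,097. The planned 1,070 lies inside this range, so it reproduces.
- At N = 1,070: 1,070 × 0.710 = about 760 deaths. The expected test statistic is ln(1.23) × √760 / 2 = 2.85, which gives 81% power at 0.05 and 68% at 0.05/3.

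**2. Thresholds.**

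- Three tests: Bonferroni 0.0167 each; Holm 0.0167, 0.025, 0.05.
- Six tests: Bonferroni 0.0083 each; Holm starts at 0.0083, then 0.01, and so on up to 0.05.
- 850,000 tests: 5.8824e-8; after 100 rejections Holm has reached only 5.8830e-8.

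The smallest p-value meets the same threshold under both methods.

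**3. Power per real effect.** Simulated, with both methods applied to the same draws. Family sizes 3 and 6 come from the article. Treating those tests as families, and every other setting, is an assumption. NC is the assumed mean of the test statistic for a real effect.

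| Family | Real effects | Bonferroni | Holm |
|---|---|---|---|
| 3 clocks, NC 2.85, correlation 0.5 | 3 | 68% | 75% |
| same | 2 | 67.8% | 71.0% |
| same | 1 | 67.7% | 67.9% |
| 6 proteins, 80% power each at 0.05, independent | 6 | 56.5% | 68.3% |
| same | 2 | 56.5% | 58.0% |
| 10 modifiers, NC 2.8 | 5 | 49.6% | 52.8% |
| same | 2 | 49.8% | 50.5% |
| 20 stage 2 markers, NC 3.3 | 10 | 61.0% | 65.0% |
| 20 stage 2 markers, NC 3.4 | 2 | 64.7% | 65.1% |
| 100 stage 2 markers, NC 3.4 | 5 | 46.8% | 47.0% |

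At 850,000 sites, a site with 80% power under Bonferroni has 80.001% under Holm after 100 rejections.

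**4. At least one, and all.** When every effect in the family is real, the chance of at least one significant result is the same under both methods: 96.1% for three independent tests and 99.4% for six, each test having 80% power at 0.05. Holm's gain lies in confirming the second and later effects. With all three clocks real at correlation 0.5, the chance of confirming all three rises from about 44% to 61%.

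**5. False positives.** With no real effects, the two methods give identical family-wise error: 4.99% for three tests and 4.95% for six. With two real clocks and one null clock, the null is falsely rejected in about 1.7% of runs under Bonferroni and 3.7% under Holm. With two real effects among six independent tests, the figures are 3.3% and 4.1%. All stay below 5%.

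**The case against.** The strongest reply is that this is a preference. Bonferroni is valid, stated in advance and conservative, and no statement in the article is wrong because of it. That stands, and it is why the point is a refinement and not an error.

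A reader might infer that single-step Bonferroni governs every analysis. The article says neither *single-step* nor *throughout*. It ties the correction explicitly only to modifiers, and it places neither the clocks nor the stage 2 markers in a corrected family.

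A reader might also infer that most markers reaching stage 2 are expected to be real, which is where Holm would help most. No section says so, and the design does not make it likely. A marker with NC 3.3 to 3.5 in 798 patients has about 1.9 to 2.0 in 272 (multiply by √(272/798) = 0.584). To carry only ten null sites out of 850,000, the stage 1 cut-off would have to be about 10/850,000 = 1.2e-5, and such a marker would pass it less than 1% of the time. Ten real markers among twenty would then need roughly 1,000 to 1,400 truly associated sites of that strength, assuming independent tests and equal effects.

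Finally, it is tempting to say that Bonferroni loses real findings for nothing. It buys something: simple simultaneous confidence intervals and a lower actual error rate when some effects are real. The loss is also negligible when few effects are real.

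**Conclusion.** The point holds as a low-priority improvement. Holm offers the same 5% guarantee and never rejects fewer hypotheses. Its benefit is 7 to 12 points of power per effect in families of three to six where all effects are real, about 3 to 4 points where half are real, and under one point in most of the settings examined with few real effects (1.5 points for two real among six). At the scale of the full array it is nil. These sizes rest on assumed family sizes, shares of real effects, effect strengths and correlations that the article does not supply. That the gain is never negative rests on no such assumption.

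The article does not support calling Bonferroni a mistake. Nor does Holm repair a different matter: N was set at an unadjusted 0.05. If the three clocks were one family, power for a given clock at the first threshold of 0.05/3 would be 66% with 733 deaths and 68% with 760, under either method.

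**What to change.** In Statistical analysis and in Strengths and limitations, replace *Bonferroni correction* with *Holm step-down (Holm-Bonferroni) procedure, applied at a two-sided family-wise alpha of 0.05 within each family of tests that is corrected*.

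This needs no patients, assays or data, only sorted p-values. The costs are that Holm has no equally simple simultaneous confidence intervals and that its actual family-wise error is somewhat higher than Bonferroni's, though still at or below 5%. If simultaneous intervals are wanted for a particular family, keeping Bonferroni there is a reasonable choice.
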